### Statistical analysis

SPSS 23.0 software is used for data analysis.For quantitative data, *t*-test and nonparametric test are used to evaluate the pairwise difference between normally distributed data and non-normally distributed data, respectively. For qualitative data, chi-square test is applied for analysis. *P* < 0.05 is considered statistically significant.Apply logistic regression model to evaluate the relative risk of each variable and its correlation with nasal polyp recurrence.Different traditional Chinese medicine syndromes are entered into a regression model, and the predictive value is determined by the area under the ROC curve (AUC). AUC > 0.9: high predictive value of the model; 0.7 < AUC ≤ 0.9: moderate predictive value. When 0.5 < AUC ≤ 0.7, the optimal diagnostic cut-off point is obtained when the Youden index (sensitivity + specificity − 1) of predictive value is maximized.

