The information obtained from traditional Chinese medicine syndrome differentiation includes symptoms, pulse patterns, and tongue patterns, which are considered subjective. However, compared to other prediction tools, traditional Chinese medicine syndrome has advantages because it does not require complex and time-consuming laboratory test for clinical prognosis or survival prediction. Scholars have found that the differentiation and classification of traditional Chinese medicine syndromes have certain significance in predicting the survival of advanced cancer patients [13]. The prognosis of primary liver cancer patients with syndrome of liver depression and spleen deficiency is the best, while the prognosis of syndrome of yin deficiency in the liver and kidney is bad [14].

Based on the main symptoms, accompanied symptoms, tongue and pulse conditions, and local examination characteristics of patients in traditional Chinese medicine, the *Otorhinolaryngology of TCM* classifies the disease into four traditional Chinese medicine (TCM) syndrome types: damp heat in the spleen and stomach, stagnant heat in gallbladder, deficiency and weak in spleen qi, and deficiency and cold in lung qi under the principles of *Otorhinolaryngology in Traditional Chinese Medicine*. In the course of clinical treatment, we have noted that the recurrence rate of patients with different TCM syndromes varies to some extent [15–18]. Previous research have indicated that the 1-year postoperative recurrence rate in patients with the types of deficiency and weak in spleen qi, and deficiency and cold in lung qi, is higher than that of patients with damp heat in the spleen and stomach and stagnant heat in gallbladder [17, 18]. After FESS surgery, although there are many factors that affect the prognosis, such as the exposure stage after discharge, living and dietary environment, and the patient's selfdiscipline. It is certain that the postoperative recurrence rate of the first two TCM syndromes is markedly higher than that of the latter two types, which occurs not an isolated case but according to some regular rules.

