### Study settings and participants

This study is still ongoing at Affiliated Hospital of Chengdu University of Traditional Chinese Medicine, and the identification of TCM syndrome types of the participants will be carried out by professional experts with TCM background. Regarding the data quality assurance of traditional Chinese medicine syndrome identification, the identification of traditional Chinese medicine syndrome types by participants will be carried out by two experts. In case of inconsistency, a third expert will be invited to join, and the final conclusion will be drawn after discussion among the three experts. The present study categorized the participants four TCM syndrome types: stagnant heat in gallbladder, damp heat in the spleen and stomach, deficiency and cold in lung qi, and deficiency and weak in spleen qi under the guide of *Otorhinolaryngology in Traditional Chinese Medicine* (Table 1) as Cohort 1, Cohort 2, Cohort 3, and Cohort 4. For eligible patients, investigators have detailed interpretation on purpose, specific content, and the designed methods on of how to complete the trial. Patients will be included in the study after the signature of informed consent.

**Table 1 Tab1:** Classification of TCM syndrome criteria

TCM syndrome types	Main symptoms	Accompanied symptoms	Tongue and pulse condition	Local examination
Stagnant heat in gallbladder	Nasal obstruction, decreasing sense of smell, bad headache, getting nasal purulence, in yellow or yellow green, in a large amount, or in odor	Whiny and irritability, mouth bitterness, throat drying, vertigo, tinnitus deafness, poor sleep	The tongue is red with yellow or greasy fur, and the pulse is rapid and profound or uneven and profound	Polyps are grayish or pale or dark red or easily bleeding and soft or tough
Damp heat in the spleen and stomach	Nasal obstruction, decreasing sense of smell, headache, runny nose, and yellow nasal discharge in a large amount	Distension and fullness in epigastric and abdominal areas, eating less, weakness and fatigue, viscous excrement	The tongue is red with yellow and greasy fur, and the pulse is rolling and rapid	Polyps are grayish or pale or dark red or easily bleeding and soft or tough

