Deficiency and cold in lung qi	Nasal congestion or light or heavy, decreasing sense of smell, lightheadedness, runny nose which is white and sticky	Onset of sneezing, shortness of breath and fatigue, low faint voice, spontaneous sweating and chills from self	The tongue is pale with thin and white fur, and the pulse is weak and slow	Polyps are white or pale in color and soft
Deficiency and weak in spleen qi	Nasal congestion, decreasing sense of smell, lightheadedness, runny nose, runny or yellow white facies	Weakness and fatigue, eating less, abdominal distension, and loose stools	The tongue is fat with dentate marks, the fur is thin and white or white and greasy or little, and the pulse is wiry and weak	Polyps are white or pale in color and soft

After being included in the study, preoperative data of all participants will be collected, including general information, medical history, TCM syndromes, VAS score of subjective symptoms, Lund-Kennedy score of nasal endoscopy, and CT scan Lund-Mackay score of sinuses. Furthermore, follow-up visits were scheduled at weeks 2 and 4 and months 2, 3, 6, 9, and 12 after surgery, and the subjective symptom VAS score and the Lund-Kennedy score will be also obtained. After the 1-year follow-up, pathological sections of the patients who completed the trial will be obtained, and the infiltration of inflammatory cells will be analyzed under a 400-fold light microscope. Then, the recurrence rate and EOS count percentage of each TCM syndrome type will be applied, and a multiple regression model will be initially established to explore the correlation among postoperative recurrence of CRSwNP and TCM syndrome types and tissue inflammatory cell infiltration types. Finally, we will establish a predictive model for CRSwNP recurrence. The flow chart of the study is presented in Fig. 1. The SPIRIT schedule of enrollment, interventions, and assessments is presented in Fig. 2.

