### Outcome measurements

Our researchers are responsible for follow-up of patients before surgery and at weeks 2 and 4 and months 2, 3, 6, 9, and 12 after surgery. After completing the 1-year follow-up, the recurrence rate will be calculated. Meanwhile, pathological sections of the patients who completed the trial will be analyzed, and the infiltration of inflammatory cells will be visualized under a 400-fold light microscope. All registered patients need to adhere to a 1-year follow-up plan before their data can be used for analysis.

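### The plan tests quantitative data pairwise at P < 0.05 with four syndrome cohorts: six uncorrected comparisons give about a 20% chance of a false positive per variable

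*Protocol article*

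**What the plan says.** Study settings and participants: "The present study categorized the participants four TCM syndrome types", labelled "as Cohort 1, Cohort 2, Cohort 3, and Cohort 4".

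Statistical analysis: for quantitative data, a t-test and a "nonparametric test are used to evaluate the pairwise difference between normally distributed data and non-normally distributed data, respectively". Qualitative data get a chi-square test. One threshold, P < 0.05, applies throughout. Recurrence is analysed by logistic regression, and the syndromes enter a regression model judged by its AUC.

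The section names no four-group test for quantitative data and no correction for several comparisons.

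The quantitative variables to which the rule could apply are:

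- **EOS percentage.** Study settings and participants reports it by syndrome type, and Primary outcome includes eosinophil infiltration in the primary question.
- **VAS and Lund-Kennedy scores.** They are recorded before surgery and again "at weeks 2 and 4 and months 2, 3, 6, 9, and 12 after surgery". Secondary outcomes gives scores secondary status.

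**The concern.** A two-group test at 0.05 keeps its error rate for that one comparison only. With four cohorts, a pairwise rule allows six comparisons per variable, and the smallest of six P values falls below 0.05 far more often than one time in twenty. The Discussion hopes to single out a certain syndrome type as prone to relapse and to link it to EOS. That is a search across groups, where a chance finding in one pair could be reported as a characteristic of a syndrome.

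A second matter concerns the two scores. The cohorts are not randomised, and Table 1 assigns them partly on symptoms and polyp appearance, so pre-operative scores may differ between cohorts. The article does not say how the pre-operative score enters the comparison of post-operative scores. This affects precision and confounding, not the number of false positives from multiple testing.

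**Working it through.** The article gives no family-wise error figure, so there is none to reproduce.

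**Inputs from the article.** Four cohorts; 0.05 per test; 200 patients in total; at least 20 per syndrome; seven post-operative visits; two repeated scores.

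**Assumptions, not in the article.** Two-sided tests; normal data; no true difference between cohorts; cohort sizes of 50 each, 20/20/80/80 or 20/40/60/80; between-visit correlation of 0.3, 0.6 or 0.8; for both scores together, a correlation between scores of 0.4.

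**1. Number of pairs.** 4 × 3 / 2 = 6.

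**2. One variable, one time point.**

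- If the six tests were independent: 1 − 0.95^6 = 26.5%. They are not, because each cohort appears in three pairs.
- For four cohorts of 50 with a pooled variance (196 degrees of freedom), each test rejects when |t| > 1.972. At least one rejects when the range of the four means exceeds 1.972 × √2 = 2.789 standard errors of a mean. The studentized range distribution for four means puts 20.2% beyond that point.
- Simulating all six t-tests gives about 20% with equal cohorts and 19.8% with each set of unequal sizes. Imbalance between cohorts hardly matters.

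**3. If every visit were tested as well.** One score gives 6 × 7 = 42 tests; both give 84. Simulated chance of at least one false positive:

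| Assumed visit correlation | One score | Both scores |
|---|---|---|
| 0.8 | about 47% | 70–72% |
| 0.6 | 58–62% | 83–85% |
| 0.3 | 73–74% | about 93% |

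**4. After adjustment.** Testing each pair at 0.05 / 6 = 0.0083 brings the simulated rate in step 2 to about 4%. Holm's first step uses the same threshold, so with no true differences its chance of any false positive is the same.

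**5. Baseline adjustment, separately.** With correlation r between pre- and post-operative score, adjustment multiplies the residual variance by 1 − r²:

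- r = 0.3: 1 − 0.09 = 0.91
- r = 0.5: 1 − 0.25 = 0.75
- r = 0.7: 1 − 0.49 = 0.51

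The values of r are assumed; the article gives none.

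**The case against.** The strongest objection is that the sentence does not name the groups compared. Taken literally, it contrasts normal with non-normal data. A before-and-after comparison is also conceivable, because the Discussion says efficacy should be judged against findings before treatment. The term for the nonparametric test is generic too. This stands as a limit on certainty. Still, the sentence ties the tests to pairwise differences, and the design is built on four cohorts, so cohort against cohort remains the natural reading.

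A second objection is that a condensed article may leave multiplicity procedures, repeated-measures models and baseline covariates to an analysis plan that is not shown. That is right for baseline adjustment and repeated measures, which are offered here only as an improvement. It does not dispose of the pairwise rule, which the article states and a later plan would have to replace.

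Four stronger readings are tempting, and the article does not support them:

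- **An error rate of 60% or so.** It requires testing at every visit and an assumed correlation of about 0.6. The article schedules data collection at those visits and does not announce tests at each.
- **Missing baseline adjustment as a cause of the inflation.** The rates above come from counting tests alone.
- **The same defect in the recurrence analysis.** Recurrence is assigned logistic regression, and the chi-square rule already allows one 4 × 2 test. Comparison of one syndrome with the rest appears only in Sample size calculation.
- **A single contrast of deficiency types against heat types as the plan's true hypothesis.** The Background reports that earlier recurrence in the deficiency types "is higher than that of patients with damp heat in the spleen and stomach and stagnant heat in gallbladder", but the stated objective concerns four types. Collapsing them would change it.

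**Conclusion.** The concern holds in a limited form. Read as cohort against cohort, the stated rule gives six uncorrected tests and about a 20% chance of at least one false positive for each quantitative variable at one time point, if the cohorts do not differ. Each single test still has a 5% error rate; it is the family of six that does not. EOS percentage by syndrome is the clearest case, because it belongs to the primary question and needs no assumption about visits.

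The range of 47% to 74% for one score is conditional on testing all seven visits and on the assumed correlations. It is not a property of the plan as written. The lack of a stated baseline adjustment is a separate matter: adjustment would remove 9% to 49% of the residual variance at assumed correlations of 0.3 to 0.7, and would reduce confounding by pre-operative severity without removing other differences between non-randomised cohorts.

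The point should be settled before analysis; it does not call the design into question.

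**What to change.** In Statistical analysis:

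1. State which groups are compared. For quantitative variables, replace the pairwise rule with a four-group test (ANOVA or Kruskal-Wallis), followed by Holm-adjusted pairwise comparisons.
2. For recurrence, use a 4 × 2 chi-square or exact test, or the overall syndrome term in the logistic model, before interpreting any single syndrome.
3. As a separate improvement, compare post-operative VAS and Lund-Kennedy between cohorts with adjustment for the pre-operative value of the same score, and name month 12 as the key time point.

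This costs a few sentences. It needs no new data, visits or patients, because the pre-operative scores are already collected. The downside is that individual pairwise P values become somewhat larger, so a real difference between two particular syndromes is somewhat harder to declare.

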## Background

Chronic rhinosinusitis with nasal polyps (CRSwNP) refers to the chronic inflammation of the sinuses and nasal mucosa, accompanied by nasal polyps. The course of the disease exceeds 12 weeks. The clinical symptoms include nasal congestion, purulent nasal discharge, sense of smell disorders, headache, and intranasal polyps [1, 2]. Functional endoscopic sinus surgery (FESS) is the major method for clinical treatment of CRSwNP when maximal drug therapy fails [3]. With the extensive development of FESS and the gradual maturity of technology and equipment, the clinical cure rate of CRSwNP has gradually improved. Despite this, there are still about 30 to 60% of patients who complain about the unsatisfactory post-surgery recovery, residual nasal discharge, and no recovery of smell. Relevant studies by DeConde A. S. have found that the recurrence rate of CRSwNP is as high as 40% at 18 months after surgery [4]. A 2-year follow-up of CRSwNP in the Chinese population has indicated the recurrence rate of 55.6% [5].

Several recent studies have shown an intimate association between the type of inflammatory cell infiltration in nasal mucosal polyps and postoperative recurrence [6–8]. The intrinsic pathological features of eosinophilic and non-eosinophilic nasal polyps affect greatly on surgical effect and post-surgery recurrence [7, 9]. Wang et al. have reported that the accuracy of eosinophil (EOS) in predicting post-surgery recurrence can be as high as 90% [7]. This is helpful for both surgeons and patients to have a more accurate judgment for the results of surgery, and corresponding individualized management plans can be designed as per the prognosis, laying a foundation for the realization of CRSwNP precise treatment. However, sufficient polyp tissues are hard to be collected when the patient is conscious, plus cell counting is time-consuming; it is therefore difficult to promote extensive clinical application under current conditions.

There is a concept of “syndrome” in traditional Chinese medicine (TCM), known as “ZHENG,” which is an important part of the theory of TCM [10, 11]. Syndrome differentiation is one of the most important concepts in the practice of TCM and comprises a series of diagnostic procedures. Syndrome differentiation is the process of comprehensive analysis of clinical information obtained by the four main diagnostic TCM procedures: observation, listening, questioning, and pulse analyses [12].

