## Methods/design

### Design overview

This study is a non-randomized, single-center, prospective cohort study, starting in January 2021, and it is currently ongoing. A total of 200 patients at 12–75 years of age who are prepared to undergo FESS will be recruited from Hospital of Chengdu University of Traditional Chinese Medicine.

Due to the similar degree of improvement in endoscopic scores and quality-of-life indicators among patients undergoing chronic sinusitis surgery at different age groups, or without exceeding the minimum clinically important differences [19–21], this study did not consider further age stratification factors. All participants are diagnosed with CRSwNP. And preoperative data will be collected, as well as follow-up visits and relevant data collection after surgery. All participants should be advised to undergo regular follow-up examinations and treatments at the hospital after surgery, regardless of their participation in our study. We are simply following up on patients.

The participants will be scheduled with follow-up at 2 weeks, 4 weeks, and 2, 3, 6, 9, and 12 months after surgery. The included patients will be assigned to different cohorts in light of corresponding TCM syndrome types and completed the 1-year-long cohort research. Before the start of this study, all researchers were trained to get familiar with the criteria of awarding scores, to improve the observation consistency of the researchers, and to ensure the reliability of the clinical research conclusions. The feasibility and accuracy of the entire process were overseen by two independent supervisors, who were responsible for inspection and confirmation of all records and reports of study data and case reports filled in correctly and completely, as well as the consistence with the original data. To ensure the follow-up visits of patients as scheduled, we will remind patients of their planned visit time via follow-up schedules, phone calls, or text messages.

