### Sample size calculation

This study includes a sample size of 200 cases. The sample size was calculated according to the recurrence rate of different TCM syndrome groups.

There are 4 exposure factors of interest in this study. In the previous study [17], the expected relative risk of the 3 exposure factors was obtained from 71 patients, and then the sample size was calculated according to each of the 3 exposure factor groups, and then the maximum of these was taken as the final sample size.

Preliminary research on four types of traditional Chinese medicine syndromes shows that the recurrence rate (relative risk) of the syndrome of spleen qi deficiency group is Pmax = 11/26 = 42.3%, the recurrence rate (relative risk) of the syndrome of dampness and heat in the spleen and stomach group is 2/32 = 6.25%, and the recurrence rate (relative risk) of the syndrome of stagnated heat in the gallbladder group is Pmin = 0/13 = 0% [17]. According to the *α* = 0.05, *β* = 0.2, and with a sample ratio of 1:2 exposed to a certain TCM syndrome characteristic group and not exposed to a certain TCM syndrome characteristic group, the sample size of each exposure factor group was calculated using PASS 11 software, following the method of sample size calculations in clinical research. Considering that the dropout rate of the research subjects is 10%, we will select the group with the largest appeal sample size. That is, the minimum sample size required for each group is 20 in the exposed group and 40 in the nonexposed group. So, to complete the observation study of four exposure factor groups, the minimum total sample size is 80 cases. The total sample size of this study is 200 cases, which meets the research requirements. It should be noted that at least 20 patients exposed to each type of traditional Chinese medicine syndrome feature need to be included in the sample. At the same time, 200 cases met the sample size of unconditional logistic regression.

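### Logistic regression is said to give relative risks, but it gives odds ratios, and on the protocol's own rates the two differ materially for the highest-risk syndrome

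*Protocol article*

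**What the plan says.** The study is a cohort with a fixed one-year endpoint. Design overview states: "This study is a non-randomized, single-center, prospective cohort study, starting in January 2021, and it is currently ongoing". Under Primary outcome, the aim is the recurrence rate one year after surgery and its correlation with syndrome type and eosinophil infiltration, leading to a predictive model.

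Statistical analysis names both the model and the effect measure: "Apply logistic regression model to evaluate the relative risk of each variable and its correlation with nasal polyp recurrence". The same section judges predictive value by the area under the ROC curve and uses the Youden index for the cut-off. The article mentions no odds ratio, no conversion to a risk ratio and no model that estimates a risk ratio directly.

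Sample size calculation uses the same term differently. It says that "the expected relative risk of the 3 exposure factors was obtained from 71 patients", but the figures it gives are simple proportions, introduced in the form "the recurrence rate (relative risk) of the syndrome of spleen qi deficiency group". They are 11/26, 2/32 and 0/13. None is a ratio of two risks. No rate is given for the fourth syndrome, deficiency and cold in lung qi.

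**The concern.** A logistic model works on the log-odds scale, so its exponentiated coefficient compares odds. Odds and risks are close when the event is rare and separate as it becomes common. The protocol expects recurrence in more than two fifths of one syndrome group, so for contrasts involving that group the choice of measure changes the reported number considerably.

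The term is also used in two ways: for an absolute risk in the sample size section and for logistic output in the analysis section. Neither is a relative risk, so a reader of the results could not tell which quantity a reported relative risk was.

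What is at stake is the stated size of the syndrome effect. The Discussion hopes to use the findings to target perioperative TCM and notes that surgeons weigh cost against benefit when prescribing it. An odds ratio of 11 read as eleven times the risk would give a wrong impression if the data showed just under seven times.

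**Working it through.** **Inputs** (Sample size calculation, from 71 earlier patients)

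- Spleen qi deficiency: 11/26 = 42.3%
- Damp heat in the spleen and stomach: 2/32 = 6.25%
- Stagnant heat in the gallbladder: 0/13 = 0%
- Lung qi deficiency and cold: no rate given

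The plan's own figures reproduce: 26 + 32 + 13 = 71, and the three percentages are correct. Pooled recurrence is (11 + 2 + 0)/71 = 13/71 = 18.3%.

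**Formulas**, with p1 the risk in the index group and p0 the risk in the reference group

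- RR = p1/p0
- OR = [p1/(1 − p1)] / [p0/(1 − p0)]
- Hence OR/RR = (1 − p0)/(1 − p1)

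The last line shows that the gap depends on both risks, so no single figure applies to every variable.

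**Contrasts that can be computed from the planning rates**

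1. Spleen qi deficiency vs damp heat. RR = (11/26)/(2/32) = 6.77. OR = (11/15)/(2/30) = 11.0. Ratio = 11.0/6.77 = 1.625, so the OR is 62.5% higher.
2. Spleen qi deficiency vs the other two groups pooled (2/45 = 4.4%). RR = (11/26)/(2/45) = 9.52. OR = (11/15)/(2/43) = 15.77. Ratio 1.656, so the OR is 66% higher.
3. Damp heat vs the other two groups pooled (11/39 = 28.2%). RR = (2/32)/(11/39) = 0.222. OR = (2/30)/(11/28) = 0.170. Ratio 0.766, so the OR is 23% lower and exaggerates the apparent protection.
4. Any group vs gallbladder heat (0/13). The reference risk and odds are both zero, so neither ratio is finite.

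**Sensitivity to the reference risk** (the reference risks here are assumptions; the protocol does not give them)

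- 42.3% vs 20%: OR/RR = 0.80/0.577 = 1.39
- 42.3% vs 30%: OR/RR = 0.70/0.577 = 1.21
- 80% vs 40%: OR/RR = 0.60/0.20 = 3.0. The 80% is the Discussion's cited recurrence probability when the eosinophil ratio exceeds 27%.

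All of these are crude two-group calculations. They show the size of the difference between the measures; they do not predict adjusted estimates.

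**The case against.** The strongest reply is that this is loose terminology. The sample size section already applies the term to plain proportions, so the analysis sentence may be no more than careless wording. Nothing in the article says that exponentiated coefficients will be published under the name of relative risk. Recurrence rates by syndrome will be calculated directly, so crude risk ratios could be read from them. Logistic regression is a conventional choice for a binary prediction model, and odds ratios are legitimate in a cohort. Crude odds ratios and risk ratios against a common reference also rank the syndromes in the same order.

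Most of that stands, and it limits the point. A reader might infer that the plan will overstate every effect by about 60%. The documents do not support that: the figure arises only in contrasts using the 11/26 group, it differs for other risk pairs, it reverses for protective contrasts, and it cannot be computed for the 0/13 group or for lung qi.

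A reader might also cite the Background, where "the recurrence rate of CRSwNP is as high as 40% at 18 months after surgery", and its 55.6% at two years, as proof that the outcome is common. Those are longer horizons than the one-year endpoint and do not establish the risk at one year. The argument needs only the 42.3%.

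What does not stand is that an unseen full plan settles the matter. The sentence pairs a named model with a measure that its coefficients do not provide. Further detail elsewhere could correct that sentence, but the sentence itself is wrong as written.

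**Conclusion.** The concern holds as a mismatch between the named model and the named effect measure. If logistic output were reported as relative risk, the effect of spleen qi deficiency against damp heat would read 11.0 where the relative risk is 6.77 on the planning rates. Other contrasts would differ by other amounts, and for protective ones in the opposite direction. This assumes that the exponentiated coefficients are what would be reported, which is the natural reading of the sentence but is not stated, and that one-year rates resemble those in the 71 earlier patients.

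A reader might infer that the main conclusion is bound to be exaggerated. The documents do not go that far. The AUC, the Youden cut-off and the tests of association do not depend on which ratio is quoted, and the predictive aim is untouched. The point should be corrected because it governs how the size of the syndrome effect is understood; it does not undermine the design.

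**What to change.** - In Statistical analysis, state that logistic regression yields odds ratios with confidence intervals, and label them so in every table.
- If relative risk is wanted, as that section says, estimate it from the cohort directly: either modified Poisson regression with robust standard errors, or standardised risks and their ratios from the logistic model with bootstrap confidence intervals. Choose one in advance.
- Plan for a syndrome group with no recurrences. None of these models gives a finite ratio against it, so report its absolute risk with an exact confidence interval. For 0/13 the exact 95% upper limit is 1 − 0.025^(1/13) = 24.7%.
- In Sample size calculation, relabel 11/26, 2/32 and 0/13 as recurrence risks and keep relative risk for ratios of two risks.

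The cost is a few changes of wording and, if risk ratios are reported, one further analysis of data already being collected. No extra patients, visits or measurements are needed.
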